#### Statistical modelling methods

Initially, the relationship between each potential prognostic factor and the failure of TER will be examined using univariable Cox regression methods. After that, we will investigate this relationship while adjusting for other prominent variables that may affect this association by using multivariable Cox regression modelling methods. Based on the results of our systematic review,^35^ we will adjust for age, sex and the indication for TER surgery.

Hazard ratios from univariable (ie, unadjusted) and multivariable (ie, adjusted) regression methods will be estimated for each prognostic factor. Flexible parametric models will be considered if the Cox proportional hazard assumptions are violated.^36^ For continuous predictors, non-linear associations between the outcome and predictors will be explored using fractional polynomial methods.

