### Participants and eligibility criteria

All patients who have given consent and have a primary TER on the NJR elbow dataset will be included in this analysis. Patients will be excluded if it is not possible to trace them after surgery, if their ID numbers are invalid or if the surgery was not performed in England.

Procedures will be excluded for the following inconsistencies in the data: (1) if a revision TER occurs before a primary TER on the same side; (2) if the procedure type reported to the NJR does not match the implant components submitted.

Eligible NJR procedures will be linked to the available HES-APC data, which include all patients’ hospital episodes from 23 October 1996 to 31 March 2022. Hospital episodes with invalid ID numbers, implausible dates or unknown discharge dates will be excluded, as will duplicate episodes.

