### Outcome measure

The primary outcome in this analysis will be the failure of TER, as indicated by the need for revision surgery recorded on the NJR. The NJR’s definition of ‘revision surgery’ will be used, which encompasses any operation involving the addition, removal or modification of one or more components in a joint replacement.^28^ This includes debridement, antibiotics and implant retention with modular exchange procedures.

The NJR elbow dataset reliably collects data on revision outcomes. Patients with joint replacements listed in the NJR are identified using national tracing services. In England and Wales, this is carried out through the NHS England’s Data Access Tracing Service. A unique national identifier is generated to link all primary and revision procedures for the same joint in a single patient. The success rate of tracing patients with joint replacements in the NJR has consistently been above 94% since 2003.^29^ Moreover, a recent national audit demonstrated high data completeness (94%) for revision TER procedures.^23^

The NJR and HES-APC data are limited by the lack of patient-reported outcomes (PROMs) as well as clinical and functional outcomes. Furthermore, it is difficult to ascertain whether patients underwent additional non-revision surgeries on the elbow. This is, therefore, a limitation of this study. These shortcomings underscore the necessity for a structured approach to collecting elbow replacement PROMs, similar to the established practices for shoulder, hip and knee replacements.

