		Comorbidities indices	HES-APC	ICD-10 codes on HES data	Continuous
	Implant-related factors	Cement type	NJR	Derived from the implant codes of submitted implants	Categorical
		Polyethylene type	NJR	Derived from the implant codes of submitted implants	Categorical
		Presence of anterior flange	NJR	Derived from the implant codes of submitted implants	Categorical
	Surgical-related factors	Funding type	NJR	Directly submitted to NJR	Categorical
		Hospital type	NJR	Indirectly derived from NJR data	Categorical
		Humeral bone grafting	NJR	Directly submitted to NJR	Categorical
		Ulnar bone grafting	NJR	Directly submitted to NJR	Categorical
		Intraoperative complications	NJR	Directly submitted to NJR	Categorical
		Surgical approach	NJR	Directly submitted to NJR	Categorical
		Region where TER was performed	NJR	Indirectly derived from NJR data	Categorical

ASA, American Society of Anaesthesiologists; BMI, Body Mass Index; HES-APC, Hospital Episode Statistics-Admitted Patient Care; ICD-10, International Classification of Diseases, 10th Revision; NJR, National Joint Registry; RHR, radial head replacement; TER, total elbow replacement.

It is important to highlight that both patients and healthcare professionals identified the volume of surgeries performed by specific surgeons and hospitals as an important potential prognostic factor that warrants further investigation. Although previous studies have explored the relationship between surgeon and hospital volume in relation to hip and shoulder replacements,^30 31^ the statistical modelling used in these analyses is complex and beyond the scope of this study. Therefore, a separate study should be conducted to examine this relationship in more detail.

The use of HES-APC data enables the investigation of comorbidities as potential prognostic factors for the first time. We will evaluate both the Charlson Comorbidity Index and the Elixhauser Comorbidity Index. The Elixhauser Comorbidity Index encompasses a wider range of comorbid conditions and is reported to more accurately predict inpatient mortality following orthopaedic surgery compared with the Charlson Comorbidity Index.^32^ However, both the NJR and HES-APC data lack information on specific conditions related to the elbow, such as stiffness, functional weakness and ulnar neuropathy. These conditions are considered important by healthcare professionals who participated in the survey and would require further investigation in a separate study using different datasets.

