If RHR was used	Categorical: yes/no	No difference
Implant stem substrate	Categorical: cobalt chrome/titanium/stainless steel	No difference
Anterior flange	Categorical: yes/no	No difference
Implant stem finish	Categorical: plasma-sprayed/PMMA-coated/beaded porous-coated	No difference
Polyethylene type	Categorical: UHMWPE/HXLPE/vitamin E-HXLPE	No difference
Cement type	Categorical: Low/medium/high viscosity Antibiotic-loaded/no antibiotics	No difference

EV, EVolution; GSB III, Gschwend-Scheier-Bähler III; HXLPE, highly cross-linked polyethylene; IBP, Instrumented Bone Preserving; MUTARS, Modular Universal Tumour and Revision System; PMMA, polymethylmethacrylate; RHR, radial head replacement; UHMWPE, ultra-high molecular weight polyethylene.

**Table 4 T4:** How surgical related prognostic factors will be measured

Variable	Data used in primary analysis	Data used in planned sensitivity analysis
Funding	Categorical: NHS/independent sector	No difference
Hospital type	Categorical: NHS/independent sector	No difference
Grade of primary surgeon	Categorical: consultant/other	Categorical: consultant/SpR/senior fellow/F1-ST2/specialty doctor/other
Region	Categorical: East of England/London/Midlands/North East and Yorkshire/North West/South East/South West	No difference
Year of surgery	Continuous/discrete: the year of surgery	No difference
Humeral bone grafting	Categorical: yes/no	No difference
Ulnar bone grafting	Categorical: yes/no	No difference
Approach	Categorical: posterior/lateral	No difference
Intraoperative complications	Categorical: none/bone penetration/fractures/neurovascular-related complication/other	Categorical: None/humeral shaft penetration/ulna shaft penetration/humerus fracture/ulna fracture/nerve injury/vascular injury/other. None/fracture or bone penetration/nerve injury/vascular injury/other.

F1, Foundation Year 1; NHS, The National Health Service; SpR, Specialist Registrar.

Most of the information pertaining to potential prognostic factors is directly submitted using the MDS forms. Additionally, several potential prognostic factors are indirectly inferred from this data, which are detailed below along with the method used to derive the data:

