#### Overall prognosis

Unadjusted net implant failure will be estimated using the Kaplan-Meier method. Unrevised TERs are either censored on 31 December 2023 or the date of death, whichever is the earliest.

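### No handling of hospital clustering is specified, so standard errors for hospital type and region, and intervals for the failure curve, are understated if hospitals differ in revision risk

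*Protocol article*

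**What the plan says.** The unit of analysis is the implant. Under Overall prognosis, "Unrevised TERs are either censored on 31 December 2023 or the date of death, whichever is the earliest". Under Participants and eligibility criteria, a procedure is dropped "if a revision TER occurs before a primary TER on the same side", a check made per elbow. Under Outcome measure, an identifier serves to "link all primary and revision procedures for the same joint in a single patient". No rule limits a patient to one TER.

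The methods named are these:

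- Overall prognosis: "Unadjusted net implant failure will be estimated using the Kaplan-Meier method".
- Statistical modelling methods: "the relationship between each potential prognostic factor and the failure of TER will be examined using univariable Cox regression methods", and then, in the multivariable models, "we will adjust for age, sex and the indication for TER surgery". Flexible parametric models are the only stated alternative, and their trigger is non-proportional hazards, not dependence between observations.

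Among the factors in Table 4 are hospital type (NHS or independent sector) and region: "Categorical: East of England/London/Midlands/North East and Yorkshire/North West/South East/South West". Under Prognostic factors to be investigated, patients and professionals are reported to have "identified the volume of surgeries performed by specific surgeons and hospitals as an important potential prognostic factor". Volume is then left to a separate study because the modelling is complex. Cluster-robust variance, frailty, random effects, stratification by hospital and bilateral cases are not mentioned.

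**The concern.** A hospital has one region and one type. All TERs done there share the same value of these factors and also share whatever else makes that hospital better or worse than average. The information on such a factor therefore depends on the number of hospitals as well as on the number of revisions. An ordinary Cox model counts only the revisions. If revision risk varies between hospitals, its standard error for hospital type or region is too small, its interval too short, and chance differences between groups of hospitals look like prognostic effects. A Kaplan-Meier interval with the usual variance has the same weakness.

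The Introduction says that knowledge of prognostic factors may help inform risk adjustment when hospital and surgeon performance is monitored. Overstated certainty about region or hospital type would be unhelpful there, although the article does not say that these two factors would be used in that way.

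**Working it through.** **Inputs from the article.** The Sample size section expects more than 3891 TERs and over 244 revisions (244/3891 = 6.27%). It states no precision, power or significance level, so there is no figure of the plan's own to reproduce.

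**Assumptions, not in the article.** Number of hospitals H; between-hospital frailty variance θ (the variance of a multiplicative hospital effect with mean 1); coefficient of variation CV of hospital size; a binary factor split 50/50. θ of 0.1 to 0.2 means that the hospital hazard has a standard deviation of √0.1 = 0.32 to √0.2 = 0.45 of its mean.

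**Step 1, independence baseline.** With D = 244 revisions, SE(log HR) = 1/√(244 × 0.5 × 0.5) = 0.128.

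**Step 2, hospital-level factor.** Design effect DE = 1 + θ × (D/H) × (1 + CV²). The true SE is √DE times the ordinary SE, and actual coverage of a nominal 95% interval is 2Φ(1.96/√DE) − 1. For H = 100, θ = 0.1, CV = 1: DE = 1 + 0.1 × 2.44 × 2 = 1.49, SE × 1.22, coverage 89.2%. The 244 revisions then carry the information of about 244/1.49 = 164.

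**Step 3, simulation.** Gamma hospital frailty, 3891 TERs, about 244 revisions, CV = 1, no true effect, 1500 runs per setting:

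| H | θ | DE by formula | SE ratio, formula | SE ratio, simulated | Coverage, simulated |
|---|---|---|---|---|---|
| 100 | 0 | 1.00 | 1.00 | 1.00 | 95.2% |
| 200 | 0.1 | 1.24 | 1.12 | 1.11 | 92.1% |
| 200 | 0.2 | 1.49 | 1.22 | 1.23 | 89.7% |
| 100 | 0.1 | 1.49 | 1.22 | 1.23 | 89.3% |
| 100 | 0.2 | 1.98 | 1.41 | 1.40 | 83.9% |

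Formula and simulation agree, and the error vanishes when θ = 0.

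**Step 4, a second simulation.** The sample is projected to the longer window, 3891 × 11.75/10.75 = 4253 TERs. The null factor is held by about 30% of hospitals, deaths are included, and there are 2000 runs per setting. A nominal 5% test rejects as follows for θ = 0, 0.1, 0.2: 4.5%, 7.4%, 11.3% with 200 hospitals; 5.0%, 12.6%, 15.6% with 100. The hospital-clustered robust test rejects 4.3 to 6.1%.

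**Step 5, wider range.** For θ 0.05 to 0.4, H 50 to 200 and CV 0 to 1, the formula gives DE from 1 + 0.05 × 1.22 × 1 = 1.06 to 1 + 0.4 × 4.88 × 2 = 4.90. That is SE × 1.03 to 2.21, and coverage from 94.3% down to 62.4%.

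**Step 6, factors unrelated to hospital.** In the first simulation, a factor assigned patient by patient has SE ratios of 0.98 to 1.02 and coverage of 94 to 96%.

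**Step 7, bilateral elbows.** DE = 1 + bρ, with b the share of TERs in pairs and ρ the within-pair correlation. For b 5 to 20% and ρ 0.05 to 0.5 (both assumed), DE is 1.002 to 1.10, so the SE grows by at most about 5%.

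The failure curve was not simulated; the direction of the error follows from the same dependence. Region has seven categories, so the binary results are an illustration for it.

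**The case against.** The strongest reply is that the point rests on silence. The article nowhere says that TERs are independent, names no variance estimator, and is a condensed account; a clustered variance may be set in a fuller plan that is not shown. This stands as a limit on what can be asserted. It does not remove the point. The article does go into analysis detail: a fallback for non-proportional hazards, fractional polynomials, imputation, recategorised factors. Followed as written, the named methods give independence-based intervals for two factors that are fixed at hospital level. A better method is available at almost no cost, and if it is already planned, one sentence settles the matter.

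Other objections succeed against stronger readings that a reader might infer:

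- *All intervals are too narrow.* They are not; Step 6 shows no material effect for factors unrelated to hospital. For a contrast within a patient, such as dominant arm in bilateral cases, ordinary intervals can even be too wide.
- *Funding, implant, cement, approach and grafting are affected to the same degree.* The article does not show that these follow unit or surgeon habit, and no partly clustered factor was simulated.
- *The plan itself expects outcome to vary between units.* It reports that others consider volume a potential factor and defers it as an exposure. That is not a statement about dependence of outcomes.
- *Null factors will be declared prognostic.* The article sets no significance rule; it says that hazard ratios will be estimated. The rejection rates in Step 4 only describe how far the intervals mislead.

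**Conclusion.** The point holds in a limited form. The article specifies no handling of clustering while testing hospital type and region. If hospitals differ in revision risk, ordinary standard errors for those two factors, and intervals for the overall failure curve, are understated.

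The direction is conditional on between-hospital variation. The size rests on assumed values: with 100 to 200 unevenly sized hospitals and a frailty variance of 0.1 to 0.2, the true SE for a hospital-level factor is about 1.1 to 1.4 times the ordinary one, and coverage is about 84 to 92%. Clustering within patients is minor over the range assumed. The matter should be fixed before analysis, but it does not undermine the study as a whole.

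**What to change.** In Statistical modelling methods, state that the Cox and flexible parametric models use robust (sandwich) standard errors clustered on the operating hospital, at least for hospital type and region and for any other factor that proves to be clustered by unit. In Overall prognosis, state that intervals for the failure curve are clustered in the same way. Add a hospital shared-frailty model as a sensitivity analysis for hospital type and region. Say in one sentence how a patient's two elbows are handled, and report the number of hospitals and of bilateral cases.

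The cost is a few sentences and a software option. A pseudonymised hospital identifier is needed. Table 1 says that hospital type and region are derived indirectly from registry data, but the article does not say whether the analysts receive an identifier, so this must be confirmed. Intervals for hospital-level factors will widen where hospitals differ. The robust variance can be unstable where few hospitals fall in one category, which may apply to the independent sector; the frailty model is a useful check there.

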**Methods and analysis:**

The primary analysis will use the NJR elbow dataset, including all eligible patients who underwent TER surgery between April 2012 and December 2023. To incorporate ethnicity and comorbidities as potential prognostic factors, the NJR will be linked to the National Health Service (NHS) England Hospital Episode Statistics-Admitted Patient Care (HES-APC) data for a secondary analysis. The analysis will adhere to the REporting recommendations for tumour MARKer prognostic studies guidelines. The primary outcome under investigation is TER failure, defined as requiring revision surgery. Initially, the overall prognosis of TER will be examined using unadjusted net implant failure via the Kaplan-Meier method. The list of potential prognostic factors to be investigated in this study has been informed by a systematic review on this topic, input from patient and public involvement and engagement (PPIE) groups and a survey shared with healthcare professionals providing TER services. The relationship between each potential prognostic factor and failure will be assessed using univariable regression methods. Based on the findings from our systematic review, the univariable association will also be adjusted for age, sex and indication for TER surgery using multivariable regression methods. The extent of missing data will be reported, and the reasons for missing data will be explored. A very high degree of data completeness is expected, and a complete case analysis will be performed as the primary analysis. Multiple imputations will be considered as a sensitivity analysis.

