## Introduction

 Total elbow replacement (TER) is a well-established treatment for painful arthritic elbows and is also used in cases of severe distal humerus fractures.^1^ TER, however, has been reported to have higher failure rates compared with other total joint replacements. It has been reported to have a 5-year failure rate of 6–10% and a 10-year failure rate of 15–19%, whereas total hip replacements have shown a 3% 5-year failure rate and a <5% 10-year failure rate.^1^,^8^ TER failure is commonly defined as the need for further elbow surgery involving the TER construct, which is widely known as revision surgery, where an implant is added, modified or removed. Revision surgery is linked to higher complication rates and poorer function than primary TER procedures.^9^

When examining factors associated with primary TER failure, a prognostic factor is defined as any variable that is associated with failure.^10 11^ Several existing studies have explored potential prognostic factors associated with the risk of failure in TER.^212^,^18^ However, a recent systematic review concluded that the current evidence on prognostic factors associated with the failure of TER is of low quality and is subject to significant risk of bias.^19^

Understanding the factors associated with TER failure could help to inform patients of the variable risks of failure and, therefore, aid decisions on whether to proceed with TER as a definitive management option.^20^ Improved understanding of prognostic factors may also reduce the need for TER revisions by enhancing treatment selection and identifying areas for innovative interventions.^10 21^ This information could also be used by government and health policymakers to identify patients at high risk, plan resource allocation and may help inform risk adjustment for monitoring hospital and surgeon performance.^10^ The James Lind Alliance, in their Priority Setting Partnership for elbow conditions, ranked research investigating the factors that affect the outcome and longevity of elbow replacements as the second most important research question in elbow conditions.^22^

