### Data sources

The analysis will use NJR data from April 2012 to December 2023. Furthermore, this dataset will be linked to the NHS England HES-APC data to supplement patient information that is not collected by the NJR, including patient comorbidities and ethnicity. The HES-APC data available for linkage only extends to 31 March 2022; therefore, the linked data will be used for a subgroup analysis. Mortality outcomes will be collected by linking the NJR data to the Civil Registrations of Death dataset. If death occurs before the revision outcome, it will be used to censor patients.

The NJR commenced the collection of data on elbow replacement procedures in April 2012. It is mandatory for all NHS and private hospitals in England, Wales, Northern Ireland, the Isle of Man and the States of Guernsey to submit data on elbow replacement surgeries, including both primary and revision procedures, to the NJR.^26^ The NJR, the British Orthopaedic Trainee Association, the British Orthopaedic Association, British Elbow and Shoulder Society (BESS) and the Royal College of Surgeons of England audited the NJR dataset in England. The TER dataset exhibited a completeness rate of 94% and an accuracy rate of over 97%.^23^ The data collected by the NJR have undergone various changes since the onset of elbow data collection, and these changes are detailed in online supplemental file 1.

The HES-APC data will be linked to the NJR data using an established process that is routinely used by NJR and detailed in a previous publication.^27^ For procedures to be linked, the start date of the HES-APC hospital episode must be the same as or before the NJR operation date, and the NJR operation date must be before or on the same day as the end date of the HES-APC episode. Access to the data and data linkage is facilitated under NJR permissions as explained in the Ethics and dissemination section.

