### Prognostic factors to be investigated

The process of selecting which potential prognostic factors to be evaluated involved conducting a systematic review to appraise existing evidence on prognostic factors associated with TER failure,^19^ collaborating with the PPIE group at Wrightington Hospital, administering a survey to communities of healthcare professionals and using the clinical expertise of the authors. The data quality for each factor will be assessed before finalising the selection for analysis. We identified 27 factors from the NJR dataset that merit investigation as potential prognostic factors and 4 from the HES-APC dataset. This includes 14 factors previously studied and 17 unexplored factors (table 1).

**Table 1 T1:** The list of potential prognostic factors that are available to be investigated on the NJR and HES-APC

Status	Type of factor	Potential prognostic factor	Data source	How are the data collected?	Data type
Factors previously investigated in the literature	Patient-related factors	Age	NJR	Indirectly derived from NJR data	Continuous
		Sex	NJR	Directly submitted to NJR	Categorical
		BMI	NJR	Directly submitted to NJR	Continuous
		Dominant arm	NJR	Indirectly derived from NJR data	Categorical
		Indication for surgery	NJR	Directly submitted to NJR	Categorical
		Ethnicity	HES-APC	Codes from medical records	Categorical
	Implant-related factors	Fixation type	NJR	Directly submitted to NJR	Categorical
		Implant linkage	NJR	Derived from the implant codes of submitted implants	Categorical
		Implant type	NJR	Derived from the implant codes of submitted implants	Categorical
		If RHR was used	NJR	Derived from the implant codes of submitted implants	Categorical
		Implant stem substrate	NJR	Derived from the implant codes of submitted implants	Categorical
		Implant stem finish	NJR	Derived from the implant codes of submitted implants	Categorical
	Surgical-related factors	Grade of primary surgeon	NJR	Directly submitted to NJR	Categorical
		Year of surgery	NJR	Directly submitted to NJR	Continuous
Factors not investigated in the literature	Patient-related factors	Weight	NJR	Directly submitted to NJR	Continuous
		Height	NJR	Directly submitted to NJR	Continuous
		ASA	NJR	Directly submitted to NJR	Categorical
		Socioeconomic status	NJR	Indirectly derived from NJR data	Categorical
		Comorbidities (osteoporosis)	HES-APC	ICD-10 codes on HES data	Categorical
		Comorbidities (diabetes)	HES-APC	ICD-10 codes on HES data	Categorical

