The collection of TER procedures on the NJR was performed using the NJR data collection tool known as the Minimal Data Set (MDS). Since the start of TER data collection, there have been 4 MDS versions, V.5–V.8. In this analysis, categorical variables will be classified based on the categories stated in the latest MDS form (MDS V.8). The measurement of each prognostic factor, including the categories to be used, is summarised in tables2^4^.

**Table 2 T2:** How patient-related prognostic factors will be measured

Variable	Data used in primary analysis	Data used in planned sensitivity analysis
Age	Continuous: measured in years	Categorical: ≥60/<60
Sex	Categorical: male/female/indeterminate	No difference
BMI	Continuous	Categorical: underweight/normal/overweight/obese/morbidly obese^41^
Height	Continuous: measured in centimetres	No difference
Weight	Continuous: measured in kilograms	No difference
Dominant arm	Categorical: yes/noPatients with unknown category will be excluded	Categorical: yes/no
ASA	Categorical: ASA1–ASA5	No difference
Indication for surgery	Categorical: Trauma/elective. Acute trauma/inflammatory/trauma sequelae/osteoarthritis/other.	No difference
Socioeconomic status	Categorical: Index of multiple deprivation quintile (V.2015)	No difference
Ethnicity	Categorical: classification is based on the ONS group classification 6a^42^Asian (includes Asian British or Asian Welsh)/black (includes black British, black Welsh, Caribbean or African)/white/mixed or multiple ethnicity/other ethnic group	No difference
Comorbidities (diabetes)	Categorical: yes/no	No difference
Comorbidities (osteoporosis)	Categorical: yes/no	No difference
Comorbidities indices	Continuous: CCI with revised weightings developed by [name] and used by the Health and Social Care Information Centre as part of the SHMI. Elixhauser Comorbidity Index.	No difference

ASA, American Society of Anaesthesiologists; BMI, Body Mass Index; CCI, Charlson Comorbidity Index; ONS, Office for National Statistics; SHMI, Summary Hospital-level Mortality Indicator.

**Table 3 T3:** How implant-related prognostic factors will be measured

Variable	Data used in primary analysis	Data used in planned sensitivity analysis
Fixation type	Categorical: cemented/uncemented/hybrid	No difference
Implant linkage	Categorical: linked/unlinked	No difference
Implant type	Categorical: Coonrad-Morrey/discovery/latitude legacy/latitude EV/latitude hybrid/GSB III/MUTARS/Nexel/IBP	No difference

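### Year of surgery is outside the fixed adjustment set, so adjusted hazard ratios for implant and surgical factors whose use changed over 2012–2023 may be confounded by calendar period

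*Protocol article*

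**What the plan says.** Under Statistical modelling methods, each factor is examined first by univariable Cox regression and then by multivariable Cox regression with a named set of adjusters: "we will adjust for age, sex and the indication for TER surgery". The set is attributed to the authors' systematic review and applies to all factors alike.

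"Year of surgery" appears in Table 1 as a surgical factor already studied in the literature. Table 4 measures it as "Continuous/discrete: the year of surgery". It is a factor in its own right, and no sentence brings it into the model for another factor.

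The cohort is all eligible patients "who underwent TER surgery between April 2012 and December 2023". Table 3 lists the implant types as "Coonrad-Morrey/discovery/latitude legacy/latitude EV/latitude hybrid/GSB III/MUTARS/Nexel/IBP". Under Overall prognosis, "Unrevised TERs are either censored on 31 December 2023 or the date of death, whichever is the earliest".

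The Introduction defines a prognostic factor as any variable associated with failure. It also names better treatment selection among the hoped-for uses of the results.

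**The concern.** Confounding by calendar period needs two things: a category whose use shifted during accrual, and a revision risk that also shifted with surgery date for other reasons, such as technique, case selection or the threshold for revising. Where both hold, the category partly marks when the operation was done, and adjusting for age, sex and indication does not remove that.

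The first condition is plausible here. The names latitude legacy and latitude EV suggest successive versions of one design, and other implant or surgical categories may also have changed over nearly 12 years. The second condition is open, but the protocol itself treats year of surgery as a possible prognostic factor.

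The risk lies in how the result is read. A newer implant could show a favourable hazard ratio, labelled adjusted, with no contribution of its own, and that figure could then inform implant choice. The modelling section describes no analysis that would separate the two explanations.

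**Working it through.** The article derives no figure on this point, so there is none to reproduce. The check asks how far the omission could move a hazard ratio, and whether adding year corrects it.

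**Inputs from the protocol article**
- Accrual from 1 April 2012 to 31 December 2023: 11.75 years.
- Expected size (Sample size section): more than 3891 TERs and over 244 revisions; 244/3891 = 6.3%.
- Common censoring on 31 December 2023 or at death.

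**Assumptions (not in the documents)**
- 4200 TERs with entry time e uniform over 0 to 11.75 years, and a death hazard of 0.05 per year.
- Revision hazard 0.0135 × r^(e − 5.875) per year, where r is the hazard ratio per surgery year. With r = 1 this gives about 260 events.
- A two-level factor, older versus newer, with a true hazard ratio of 1.00. The probability of the newer level is 1/(1 + exp(−s(e − 5.875))), with s = 0.3 (gradual uptake) or 0.8 (steep uptake).
- Cox models with and without e, 60 replicates per scenario.

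**Results for the factor with no effect**

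| Uptake | r per year | HR without year | HR with year | SE ratio, with/without |
|---|---|---|---|---|
| Gradual | 1.00 | 0.97 | 0.97 | 1.08 |
| Gradual | 0.97 | 0.92 | 0.96 | 0.98 |
| Gradual | 0.95 | 0.91 | 0.98 | 1.05 |
| Gradual | 0.90 | 0.85 | 1.02 | 1.11 |
| Steep | 1.00 | 0.99 | 1.00 | 1.23 |
| Steep | 0.97 | 0.88 | 0.98 | 1.32 |
| Steep | 0.95 | 0.81 | 1.01 | 1.24 |
| Steep | 0.90 | 0.67 | 0.98 | 1.14 |

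The figures carry simulation noise of a few hundredths: the first row shows 0.97 where the truth is 1.00. Dividing the two hazard ratios within a row removes much of the noise they share. This gives 0.92/0.96 = 0.96, 0.91/0.98 = 0.93 and 0.85/1.02 = 0.83 for gradual uptake. For steep uptake it gives 0.88/0.98 = 0.90, 0.81/1.01 = 0.80 and 0.67/0.98 = 0.68. A mild trend with gradual uptake therefore matters little, and a strong trend with steep uptake matters a good deal.

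**Unequal follow-up alone.** In the steep, r = 1.00 row, median follow-up is 6.8 years in the older level and 2.5 in the newer. The crude risk ratio is 0.45, yet the Cox hazard ratio is 0.99. Staggered entry by itself does not bias the planned analysis.

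**Non-proportional effect.** If the factor's hazard ratio is 1.0 before 4 years and 2.0 after, with steep uptake and no calendar trend, the single Cox hazard ratio is 1.22 without year and 1.35 with year. The summary then depends on the follow-up mix, and adding year does not cure that.

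**The case against.** The best defence is that the study is prognostic. An association not adjusted for year is still a valid association under the Introduction's definition, and the adjustment set is prespecified from a systematic review that had literature on year of surgery available. This stands as far as it goes: the planned model is not wrong and should stay. It does not cover the stated treatment-selection use, where a reader will take an adjusted hazard ratio as the factor's own contribution.

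A second objection also stands. The documents show neither a calendar trend nor a link between category and year, and the steep-uptake scenarios are close to complete separation by date. The bias can be called possible, not present. Nor does the point reach surgical factors whose use was stable.

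Some stronger readings are tempting but unsupported:
- **Follow-up must be equalised or truncated.** Kaplan-Meier and Cox methods handle staggered entry through risk sets, as the check shows. Truncation would discard late failures. Follow-up mix matters only if hazards are non-proportional, and there the protocol says flexible parametric models will be considered.
- **About half of ten-year failures come after year 5.** The Introduction cites a "5-year failure rate of 6–10% and a 10-year failure rate of 15–19"%. The late share depends on how the ends of the ranges are paired, from (15 − 10)/15 = 33% to (19 − 6)/19 = 68%. No single figure follows.
- **Changes in data collection distort the implant comparisons.** The article says that "The data collected by the NJR have undergone various changes since the onset of elbow data collection". However, every implant factor except fixation type is derived from component codes, and categorical variables are to be classified by the latest form.

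**Conclusion.** The point holds in limited form. The fixed adjustment set omits year of surgery, which the protocol collects and itself regards as possibly prognostic. Adjusted hazard ratios for implant factors, and for surgical factors whose use changed during accrual, may therefore be confounded by calendar period.

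The size rests wholly on assumed trends and uptake. With a 3% to 10% yearly fall in hazard, a null factor would show about 0.92 to 0.85 under gradual uptake and 0.88 to 0.67 under steep uptake. A rising hazard would push the other way, and with no trend there is no bias. This is a change worth making before analysis, not a flaw that invalidates the plan.

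**What to change.** For implant factors, and for surgical factors whose use changed between April 2012 and December 2023, keep the age, sex and indication model. Beside it, report a second Cox model that adds year of surgery as a continuous term, non-linear if needed. State the range of follow-up observed in each category, so that a hazard ratio for a recent category is not read as covering years it has not been observed.

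Where categories were not all in use throughout, an analysis restricted to the overlapping calendar years may be added as a sensitivity analysis. It will rest on fewer events.

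The cost is protocol or analysis-plan wording and extra model runs on data already held. A linear year term adds one parameter against more than 244 expected revisions; a non-linear form adds more. In the simulation the standard error of the log hazard ratio changed by a factor of about 1.0 to 1.1 with gradual uptake and 1.1 to 1.3 with steep uptake. Where category and year nearly coincide the year-adjusted estimate will be imprecise, and the report should say so.
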